**Benefits/Impacts**

The primary benefit of involvement in this project is the anticipated mental health and wellbeing of participants. The overall aim of Vitalk is to improve wellbeing by reducing stress, anxiety and depression using a preventative approach to mental health, which the participants shall benefit from. Additionally, the participants will also benefit from the mental health presentations to be conducted at the workshops, in which the members of the Department of Psychology shall discuss various aspects of mental health and how it affects workplace performance and wellness.

Participants will receive an allotment of 10Gb data bundle allowance valued at K15,500 (about $20) with a selected mobile carrier to eliminate any barriers of accessing the internet during the trial. Those not using the preferred provider at the time of the trial will receive a free SIM card. If it is feasible for the mobile service provider to track whether Vitalk or the control group website were accessed, airtime allocations will be contingent on the use of Vitalk or the control group website. In addition, all participants will be reimbursed $10 for their transport and time, as well as the government rate lunch allowance of K4000 during the attendance of the introductory and concluding workshops.

In addition, and following common practice in clinical trials, participants will receive an appreciation allocation of about 5Gb airtime valued at K8,200 (about $10) at the end of the trial, the final workshop, in recognition of their time sacrifice and as appreciation of their contribution to science. This incentive will hopefully encourage participants in the treatment group to continue the use of the Vitalk app and participants in the control group to try out Vitalk.

1. **Research dissemination strategy**

The results of this study will be published in an international, peer-reviewed journal and a copy will be submitted to UNIMAREC. These results can also be presented at relevant research conferences, whether local or international. The results of this research will also be disseminated through presentations in fora that will inform policy at a national level and health system strengthening approaches supported by development organizations such as USAID, Chemonics and University Research Co. (URC), and academic institutions such as the University of Malawi. The focus will be on strengthening of mental health services refining and expanding the use of virtual, online tools and innovations.

1. **Ethics**

The study will be conducted with full adherence to ethical standards as expressed in the APA Code of Ethics on psychological research, as well as the Declaration of Helsinki. Before commencement of the study, relevant authorization will be sought from University of Malawi Research Ethics Committee (UNIMAREC). Participation in the study will be voluntary and participants will be informed of this, and that they may withdraw at any time of the study. Participants who agree to participate in the study will be informed clearly what the study is about and how their information will be used. Informed consent will be obtained online upon registration at the study web-portal. All forms will be printed and kept in a locked cabinet at the Department of Psychology, UNIMA.

1. **Workplan**

**
[figure not shown]
**

References

Beck J.S. (2011) Cognitive Behaviour Therapy, Second Edition: Basics and Beyond. New York, NY: Guilford Press.

**APPENDIX A: CONSENT FORMS AND DATA COLLECTION TOOLS**

- 1. **Data collection instruments**

Annex 1.2.1

**Screening questionnaire (online)**

1. What type of health worker are you? *Please select*
   1. Doctor
   2. Nurse
   3. Clinical officer
   4. Medical Assistant
   5. Physiotherapy technician
   6. Laboratory technician
   7. Pharmacist
   8. Other
2. English language proficiency
   1. Fluent
   2. Some proficiency
   3. None
3. Do you own a smartphone?
   1. Yes
   2. No
4. Are you using TNM as a service provider?
   1. Yes
   2. No
5. Are you currently being counseled or treated for mild or moderate mental health issues?
   1. Yes
   2. No
6. Are you currently being counseled or treated for acute or severe mental health issues?
   1. Yes
   2. No
7. Do you have suicidal thoughts?
   1. Yes
   2. No

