4.1. Study Design, Randomization, And Blinding

This study is guided by the conceptual framework shown in Figure 1 below. The study is a two-arm, parallel randomized controlled trial with a pre-treatment assessment, 8-week intervention period and mid-study assessments at 4-5 weeks and an end-of-study assessment at 9 weeks^^[[1]](#footnote-1)^^. Interested study participants will be randomly assigned to either the treatment or control group at the time of registration. Vitalk, the developer of the app, will create a study web portal where study participants register, give their consent, are assigned to one of the study arms, are given a unique study identification number, and enter their demographic information. Depending on the random assignment, participants will be taken to either the treatment app, Vitalk, or the website for the control group. This is a single blinded design because only the research team will be blinded to the study arm assignments; all participants in both study arms will be told they are participating in ‘*an online self-help for mental wellbeing*’.

[figure not shown]

*Figure 1. Study framework*

Participants will be required to seek approval from their employers to participate in the study, because some activities will occur during working hours, but no information collected during the trial that could identify participants or their facilities of affiliation will be shared with the employers. A trial manager, someone appointed by Vitalk and the Department of Psychology (UNIMA) who is not part of the research team, will provide technical support in case participants encounter difficulties with the study portal or the Vitalk app and be therefore privy to the group assignment, but this information will not be shared with the research team during the study. The study portal and control group website will be optimized for and accessible through smartphones. Vitalk is a smartphone app for Android and iOS.

- 1. Treatment and control group interventions
[figure not shown]

     1. Vitalk chatbot app (treatment group, *active*)

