**Study participants**

Study participants will be recruited from all primary, secondary and tertiary care facilities within Blantyre and Lilongwe districts.

Inclusion criteria are as follows:

- Type of service provider (cadre)
- English language fluency
- Smartphone ownership
- No or current CBT for mild or moderate mental health disorders
- No suicidal ideation
- Initial mental health test scores below severe levels

The participants of this study will be health workers of the following professional cadres from health facilities:

| - Doctors | - Nurses |
| --- | --- |
| - Medical Assistants | - Clinical officers |
| - Laboratory technicians | - Physiotherapy technicians |
| - Pharmacists |  |

The minimum required educational qualification is a diploma in their respective fields of specialization, in adherence to the Ministry of Health employment criteria for the respective cadres of health workers. However, Medical Assistants who completed 2 years of college will be allowed to participate even though their qualification is a certificate. These selection specifications are put in place based on the general assumption that such participants are competent in the English language as a medium of communication, which will facilitate their interactions with the Vitalk App and the mental health resource website since all the interactions on these platforms are in English. Additionally, study participants are expected to own a smartphone on which they can download and use the Vitalk App and access the mental health resource website, which is an additional reason for limiting participant selection to the above cadres.

Exclusion criteria for this study includes all other hospital- or health-related personnel, such as health surveillance assistants, hospital assistants or laboratory assistants, due to their lower educational qualification requirement for employment. In addition, considering that smart phones are not very widely available within many social circles in Malawi and are considered to many as a luxury, this research assumes that cadres listed above have a higher chance of owning a smart phone due to their higher grade of pay than those of lower employment cadres.

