**Sampling method**

Study participants will be recruited from all primary, secondary and tertiary care facilities within Blantyre district on a first come-first served basis. While this is a convenience sample based on self-selection, random assignment to treatment and control groups will counteract biases inherent to this approach. All participants are volunteers and agree to be assigned to either the treatment or the control group.

The required study population size for paired tests of correlated means was calculated using STATA 17 and is based on the following:

- Pre-post-treatment difference of 1.5 points on standard test scales
- Standard deviation of the difference = 6
- Power 80%
- Significance level 5%

This results in a minimum of 128 participants per study arm. Given the continuity experience – the proportion of participants completing the pre- and post-treatment assessments for depression, anxiety and stress – of 20-45% reported by Daley, Hungerbuehler et al. (2020), we assume that the dropout rate will be as high as 75% for at least one of the standard mental health assessments. This means that a sample of 512 participants will be required per study arm to yield an effective post intervention sample of 128. Furthermore, if 20% of potential study participants will not meet inclusion criteria or drop out for other reasons, about 640 people will need to be recruited initially per study arm. Therefore, the total number of participants for this study is 1280.

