Annex 1.2.3

**Data collected by the website for the control group and Vitalk for the treatment group**

1. Completed registrations (enrollment)
2. Completed GAD-7 and scores
3. Completed PHQ-9 and scores
4. Completed RS-14 and scores
5. Completed OLBI and scores
6. Frequency of use and results of Mood Meter
7. Completed resilience-building behavior assessment and results
   1. Frequency of Engaging in Cognitive Behavioral Stress Mgm’t over last 2 weeks
   2. Frequency of Practicing Mindfulness and Relaxation over last 2 weeks
   3. Frequency of Practicing Self-care over last 2 weeks
   4. Frequency of Connecting to Purpose over last 2 weeks
   5. Frequency of Connecting to Others over last 2 weeks
8. Program selected or clinical content accessed in Vitalk or pages accessed and links followed on control website
9. Frequency, timing and duration of interaction with control website or Vitalk
10. Number and frequency of questions asked
11. Number and frequency of no access to the internet
12. Number and frequency of technical support requested

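### Screening checks only that applicants own a smartphone, not that it can run Vitalk, so any installation failure would arise after allocation and in the treatment arm alone

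*Combined protocol and SAP*

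**What the plan says.** The bulleted inclusion criterion under Study participants is ownership of a smartphone. The paragraph below it goes further: participants are expected to "own a smartphone on which they can download and use the Vitalk App" and to reach the control website with it.

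The screening questionnaire (Annex 1.2.1) puts this into practice as item 3, a yes/no question: "Do you own a smartphone". Item 4 asks about the mobile carrier. Nothing there, or in the participant characteristics questionnaire (Annex 1.2.2), asks about operating system, version or ability to install an app.

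Section 4.1 states that "Vitalk is a smartphone app for Android and iOS", that assignment happens at registration, and that the portal and control website are built to work on smartphones. The description of the interventions gives Vitalk to the treatment arm only. Under Study period, the link to Vitalk or to the website is emailed after the introductory workshop.

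Annex 1.2.3 is headed "Data collected by the website for the control group and Vitalk for the treatment group" and lists completed scores on all four scales among those data.

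**The concern.** The text expects a phone that can take the app, but the step that admits people does not test for one. The first test comes when a treatment participant tries to install Vitalk, after allocation. A control participant with the same phone only has to open a website, so the failure cannot occur in that arm.

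Three things are at stake.

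- **Dilution.** Treatment participants who cannot install the app receive no chatbot, which pulls the between-arm difference towards zero.
- **Possible arm-specific missing data.** Annex 1.2.3 places treatment-arm scores in Vitalk, so some scores might be lost in that arm only. The plan names no analysis population and has no rule for people who cannot install the app.
- **Misread adoption.** Objective 1 concerns engagement and continuity of use. An unsuitable device would be counted as poor uptake of the product.

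**Working it through.** **Order of events.** Section 4.1 and Study period together give: screening on ownership, registration with allocation, then the app link by email. No check of the device against the app is described before allocation.

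**The plan's own sample size.** Inputs from Sampling method: "Pre-post-treatment difference of 1.5 points on standard test scales"; "Standard deviation of the difference = 6"; power 80%; significance level 5% (sidedness not stated, two-sided assumed); a paired test.

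- Normal formula: n = [SD × (z for 0.975 + z for 0.80) / difference]² = [6 × (1.960 + 0.842) / 1.5]² = 125.6, so 126.
- Noncentral t: n = 128, with power 0.802. This is the stated figure.
- Inflation: 128 / (1 − 0.75) = 512; 512 / (1 − 0.20) = 640; 2 × 640 = 1280. All reproduce.

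Both allowances (75% and 20%) are the same in each arm, so neither provides for a loss in one arm only.

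**Effect of incompatible phones.** Let x be the share of owned smartphones that cannot run Vitalk. The documents do not give x; the values below are assumptions. Installation failure is taken as unrelated to other dropout, and power uses the number of completers rounded down.

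| x | Affected of 512 (512x) | Treatment completers, 128(1 − x) | Completers affected (128x) | Paired power if lost | 1.5(1 − x) if kept with no benefit |
|---|---|---|---|---|---|
| 0 | 0 | 128 | 0 | 0.802 | 1.50 |
| 2% | 10.2 | 125.4 | 2.6 | 0.792 | 1.47 |
| 5% | 25.6 | 121.6 | 6.4 | 0.779 | 1.425 |
| 10% | 51.2 | 115.2 | 12.8 | 0.758 | 1.35 |
| 20% | 102.4 | 102.4 | 25.6 | 0.706 | 1.20 |

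The last column shows proportional shrinkage only. The plan's 1.5 points is a within-arm pre-post change, so the column should not be read as a between-arm intention-to-treat difference. At 5-10% the shrinkage is 0.075-0.15 points, or 0.0125-0.025 of the SD of 6.

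**Would over-recruiting help?** Allocating 512 / 0.95 = 539 or 512 / 0.90 = 569 to the treatment arm would bring completers back to 128. It would not remove the imbalance between arms.

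**Routes to outcome data.** Annex 1.2.3 points to Vitalk for the treatment arm. Under Study period, however, baseline tests follow registration on the study portal before any app link is sent, the mid-trial request goes to all participants by email, and the final tests are taken at a week-nine workshop to which both arms are invited. Someone without the app therefore has a baseline and a possible week-nine assessment.

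**The case against.** The strongest reply is that criterion and screening item agree: both say ownership. The text about running the app is explanatory, and its stated use is to justify limiting recruitment to certain cadres, which item 1 does screen. No section mentions an incompatible phone, a minimum version or an installation failure. Technical support is provided, support requests are logged, and the closing questionnaire and focus groups ask why the app was little used. Set against a planned 75% dropout, a few percent is small. Asking about the phone system also hints at an app, when the plan withholds intervention details.

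Much of this stands, and it rules out several stronger readings.

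- A reader might infer that a formal criterion is being misapplied. The listed criterion is ownership; app capability is an expectation in the surrounding text.
- A reader might infer that incompatible phones are in fact being allocated. The documents show only that they can be.
- A reader might infer that treatment participants without the app have no means of giving scores. The portal baseline, the emailed mid-trial request and the week-nine workshop contradict that.
- A reader might infer that people who cannot start are excluded from analysis. No such rule appears.

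The reply does not remove the gap. Support acts after allocation and cannot make an unsupported phone compatible. The logs and questionnaires may help explain low use, but they do not prevent dilution. The hint to participants is slight, because a question on phone system names no intervention.

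**Conclusion.** The point holds in a limited form. The plan expects a phone able to run Vitalk, tests only ownership, and sends the app link after allocation, so any installation failure falls on the treatment arm alone. The size depends on an undocumented share of phones. At an assumed 5-10%, benefit is diluted by that same proportion if those affected are kept, and within-arm paired power falls from 0.80 to about 0.78-0.76 if they are lost. Whether the result is dilution or missing data is unsettled, because it depends on follow-up and on an analysis population the plan does not name. The figures 128, 512, 640 and 1280 are unaffected. The effect is modest, but it is worth correcting because a one-arm problem created after randomization cannot be fully repaired in analysis.

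**What to change.** - Extend item 3 of the screening questionnaire to ask every applicant for phone system (Android / iOS / other) and version, before allocation and without naming Vitalk.
- Obtain the app's minimum requirement from the developer, since the documents do not give it, and apply it identically to all applicants. A phone that falls short makes the applicant ineligible whichever arm would have followed.
- State in Study participants that this is a criterion, so that the list, the explanatory text and the form agree.
- State in Data analysis method that everyone allocated is followed up and analysed as randomized, including anyone who still cannot install the app.

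The cost is an extended screening item and two sentences. A few people who could have used the control website become ineligible; they fall under the existing 20% allowance for ineligibility and other losses, though whether it has room for them is unknown. The question also gives a slight hint that an app may be involved.

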Annex 1.2.2

**Participant characteristics questionnaire (online)**

1. How old are you? *in years*
2. What is your gender:
   1. Male
   2. Female
   3. I prefer not to disclose
3. At what type of health facility do you work?
   1. Tertiary/central hospital
   2. Secondary/district hospital
   3. Primary care facility (clinic, health center, community and rural hospital, maternity unit)
4. What type of facility is it?
   1. Public/government
   2. Private-not-for-profit (for example, CHAM)
   3. Private-for-profit
5. Where is your facility located?
   1. Urban
   2. Peri-urban
   3. Rural
6. In which district is your facility located?
   1. Blantyre
   2. Other _____________________
7. What is the main area in which you work? *Single choice*
   1. Counseling
   2. Dental care
   3. Emergency care
   4. General inpatient care
   5. Intensive care
   6. Laboratory services
   7. Maternity care
   8. Mental health care
   9. Neonatal care
   10. Outpatient care
   11. Pediatric care
   12. Physiotherapy
   13. Radiology services
   14. Surgical care
   15. Other
8. I use my smartphone for: *check all that apply*

*How often (one check per row): Daily Several times a week Weekly Less often Never*

- 1.
[figure not shown]

[figure not shown]

[figure not shown]

[figure not shown]

[figure not shown]

[figure not shown]

[figure not shown]

[figure not shown]

[figure not shown]

[figure not shown]

[figure not shown]

[figure not shown]

[figure not shown]

[figure not shown]

[figure not shown]

[figure not shown]

[figure not shown]

[figure not shown]

[figure not shown]

[figure not shown]

[figure not shown]

[figure not shown]

[figure not shown]

[figure not shown]

[figure not shown]

[figure not shown]
Browsing the internet
  2.
[figure not shown]

[figure not shown]
Calling, texting, WhatsApp
  3.
[figure not shown]

[figure not shown]
Facebook, Twitter
  4.
[figure not shown]

[figure not shown]
Interactive chat apps
  5.
[figure not shown]

[figure not shown]

[figure not shown]
Mobile Money
  6.
[figure not shown]
Playing games
  7.
[figure not shown]

[figure not shown]
Reading and sending email
  8.
[figure not shown]

[figure not shown]
Watching videos/movies,
     listening to music
  9.
[figure not shown]
I don’t have a smartphone

1. Are you currently in therapy or have you had therapy in the past for mental health issues? *Select one*
   1. Currently in therapy
   2. Had past therapy during the last 6 months
   3. Had past therapy during the last 2 years
   4. Had past therapy more than 2 years ago
   5. Never had therapy
2. Social relationships: please answer a few more questions about your relationships with others. Remember, when the term “others” is used, it includes friends, neighbors, or family members. Check the circle that represents your response. *One check mark per row*

|  | *Never*  *1* | *Once in a while*  *2* | *Fairly often*  *3* | *Very often*  *4* |
| --- | --- | --- | --- | --- |
| 1. In general, how often do you feel that you lack companionship? |  |  |  | [figure not shown][figure not shown][figure not shown][figure not shown] |
| 1. In general, how often do you feel left out? | [figure not shown][figure not shown][figure not shown][figure not shown] |  |  |  |
| 1. In general, how often do you feel isolated from others? | [figure not shown][figure not shown][figure not shown][figure not shown] |  |  |  |

Annex 1.2.3

**Data collected by the website for the control group and Vitalk for the treatment group**

1. Completed registrations (enrollment)
2. Completed GAD-7 and scores
3. Completed PHQ-9 and scores
4. Completed RS-14 and scores
5. Completed OLBI and scores
6. Frequency of use and results of Mood Meter
7. Completed resilience-building behavior assessment and results
   1. Frequency of Engaging in Cognitive Behavioral Stress Mgm’t over last 2 weeks
   2. Frequency of Practicing Mindfulness and Relaxation over last 2 weeks
   3. Frequency of Practicing Self-care over last 2 weeks
   4. Frequency of Connecting to Purpose over last 2 weeks
   5. Frequency of Connecting to Others over last 2 weeks
8. Program selected or clinical content accessed in Vitalk or pages accessed and links followed on control website
9. Frequency, timing and duration of interaction with control website or Vitalk
10. Number and frequency of questions asked
11. Number and frequency of no access to the internet
12. Number and frequency of technical support requested

